### Statistical issues

#### A. Sample size and the detectable difference

Because patient function (or dysfunction) is generally considered the more consequential of our two primary outcome measures [27] (the other being bothersomeness of back pain), sample size calculations are based on the Roland-Morris Disability Questionnaire (RDQ). Our sample size is designed to ensure that we have good power to detect a clinically significant difference of 2.5 points for pairwise comparisons (yoga to self care and yoga to exercise) on the RDQ (Aim 1 and 2) and adequate power to detect a difference of 1.7 points between the yoga and exercise groups that would be of interest when exploring mechanisms of action (Aim 3). We think that a smaller detectable difference between yoga and exercise can be justified when examining mechanisms of action because in the Aim 3 comparison of yoga and exercise, we focus on the *additional *benefits of yoga compared with exercise, anticipating that a portion of yoga's clinical effects would actually result from movement.

We have accommodated these dual power needs by proposing a 2:2:1 randomization ratio (yoga: exercise: self care), with a total of 210 participants. Assuming 10% loss to follow-up (which is slightly higher than in our previous study [19]), there would be outcomes data for 75:75:38 participants in the yoga, exercise, and self care groups, respectively. To protect against multiple comparisons, we will use Fisher's protected least significant difference approach, which has been shown to have desirable properties when there are three groups [51]. This approach makes pair-wise comparisons between the three treatment groups only if the overall *F*-test is significant. The power of this omnibus *F*-test depends on how the means from the three treatment groups differ. We therefore assumed that the yoga group would be 1.7 RDQ points superior to the exercise group, which would, in turn, be 0.8 RDQ points better than the self care group (giving a difference of 2.5 points between the yoga and self care groups). We chose a 1.7-point difference between yoga and exercise because it is slightly more conservative (i.e., smaller) than that found in our previous study [19].

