Our estimates of the standard deviations of our primary outcome measures adjusted for pre-randomization baseline values were derived from analyses of covariance of 12-week follow-up data estimated from the 101 study participants in our 3-arm pilot study: RDQ standard deviation (SD) = 3.68 and bothersomeness SD = 2.38. With our proposed sample size, the omnibus *F*-test for the RDQ score will have 92% power for detecting a statistically significant difference among the three treatment means with the distribution assumed above. If this omnibus test isstatistically significant we will address Aims 1 and 2 of the study by comparing the appropriate pairs of means, as discussed below. To detect a pair-wise difference of 2.5 RDQ points, we will have 92% power for the yoga (or exercise) to self care comparison and 98% power for the yoga to exercise comparison. For Aim 3 we will have 92% to detect a pairwise difference of 2.5 RDQ points between yoga (or exercise) and self care and 80% power to detect a pairwise difference of 1.7 points between yoga and exercise.

Our sample size will also provide adequate power to detect a clinically important difference of 1.5 on our 0 to 10 bothersomeness measure. For the omnibus *F*-test, we will have 89% power for detecting a significant difference of 1.5 points among the three groups (if we assume a difference of 1.1 points between the yoga and exercise groups and of 0.4 points between exercise and self care). For a difference of 1.5 points on the bothersomeness measure, we will have 88% power for the yoga (or exercise) to self care comparison and 97% power to for the yoga to exercise comparison. For Aim 3, we will have 88% power to detect a pairwise difference of 1.5 bothersomeness points between yoga (or exercise) and self care and 80% power to detect a pairwise difference of 1.1 points between yoga and exercise.

At each time point, both primary outcomes (function and symptoms) will be tested at the 0.05 level because they address separate scientific questions. Analyses of both outcomes at all follow-up times will be reported, imposing a more stringent requirement than simply reporting a sole significant outcome. Arguments against adjusting for multiple comparisons in this situation have been made by Rothman [52,53] and others [54].

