The power calculations are based on simple comparisons of the follow-up scores at a single point in time with adjustment for baseline values using analysis of covariance. We also plan to adjust for other baseline characteristics (e.g., age, gender, and baseline covariates found predictive of 10-week outcomes). Inclusion of such baseline covariates can improve precision of the variance estimate and therefore increase power.

Since assessment of Aim 3, the mediator analysis, is dependent on the results from Aim 1 and Aim 2, the study was not directly powered for Aim 3. We ran a simple power analyses for the primary mediator of interest, body awareness, assuming the expected sample sizes of 75:75:38, a single time point, and the RDQ Score as the outcome. We found a median power of 0.86 to detect body awareness as a significant mediator for yoga compared to self care and a median power of 0.83 for to detect body awareness as a significant mediator for yoga compared to exercise.

In summary, we have excellent power to detect a clinically meaningful difference on the omnibus test and the pairwise comparisons with self care for Aims 1 and 2 as well as adequate power to evaluate the yoga - exercise comparison for the mediator analysis for Aim 3. Although powered to detect a clinically significant difference on the RDQ, the resultant sample sizes will provide ample power for both of our primary outcome measures.

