After determining the subset of mediators to be included from each class, we will run a final multiple mediator IPW model. The application of the IPW approach, as compared to the traditional approach of adjusting for multiple mediators, allows us to more appropriately account for confounding between a mediator and the outcome both by additional mediators and by other measured variables [60]. Further we are better able to estimate the indirect effects of each mediator in a causal framework through decomposition of the total effect of treatment into indirect effects through each mediator and the direct effect after accounting for all mediators.

All time points for which there is a significant difference between yoga and self care (or exercise) will be included in the models, and we will use GEE to account for possible correlation within subjects over time.

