The results of our previous study suggest that there are several possible scenarios of treatment differences we might expect to find in our proposed trial [19]. Each of these scenarios would result in a different approach to exploring mediating factors. *Scenario 1: *yoga is more effective than self care but not significantly better than exercise, which is not significantly better than self care. In this scenario, we will look for mediators that explain the mechanisms through which yoga works compared to self care, but we cannot explore whether there are different mediators for exercise and yoga if exercise is not significantly better than self care. Thus, we will not be able to determine whether there are mechanisms of healing unique to yoga compared to a "body-focused" treatment like exercise. *Scenario 2: *yoga is significantly better than both self care and exercise, and exercise may or may not be significantly better than self care. In this scenario, we will look for mediators that may explain how yoga works compared to self care and to exercise. It is possible that these mediators are different. By focusing on the yoga vs. exercise difference, we can determine which mediators are most responsible for the unique effects of yoga, which we believe will be mostly those related to increased awareness. *Scenario 3: *both yoga and exercise are better than self care but yoga is not significantly different from exercise. In this scenario, we might conclude that the beneficial effects of yoga are solely or largely due to physical exercise, and that the awareness component has no materially important effect on back pain. However, it is possible that completely different pathways mediate these beneficial effects, and we will be able to determine this through the mediator analysis. For example, the treatment effect of yoga compared to self care might be significantly reduced when a specific mediator variable (e.g., body awareness) is included in the model, with no significant change on the treatment effect of exercise compared to self care.

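### Scenario 3 infers different pathways for yoga and exercise from one significant and one non-significant mediator result, without comparing the two indirect effects

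*Protocol article*

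**What the plan says.** The mediator analysis is described in the Protocol article under Statistical issues, B. Statistical analysis. Candidate mediators are screened against treatment group at an alpha of 0.10 and ranked by how much of the treatment effect each explains. Those that explain at least 10% are kept and entered in a final inverse-probability-weighted model that splits the total effect into direct and indirect parts. On time points, the section says: "All time points for which there is a significant difference between yoga and self care (or exercise) will be included in the models".

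The same section then sets out three scenarios. Of Scenario 3 it says that "it is possible that completely different pathways mediate these beneficial effects, and we will be able to determine this through the mediator analysis". It gives one example of how this would show: adding a mediator such as body awareness significantly reduces the yoga v self care effect, "with no significant change on the treatment effect of exercise compared to self care".

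On power, section A (Sample size and the detectable difference) says: "We found a median power of 0.86 to detect body awareness as a significant mediator for yoga compared to self care". It also gives 0.83 for yoga v exercise. It gives no mediation power for exercise v self care, and it says the study was not directly powered for Aim 3. The Background calls the model testing exploratory.

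**The concern.** The example compares two separate significance verdicts. Its second half takes a non-significant mediator result for exercise v self care as a sign that exercise does not act through that mediator. A true indirect effect of the same size in both arms can be significant in one and miss significance in the other by chance alone. The quantity that answers the question is the difference between the two indirect effects, and the text names neither a test nor an interval for it.

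The yoga v exercise mediator analysis does not fill the gap. The protocol describes it for Scenario 2, and the time-point rule admits only time points with a significant difference. Scenario 3 is defined by the absence of a significant yoga–exercise difference.

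At stake is how Aim 3 would be read. The mechanism work is meant to guide later studies, and a pathway wrongly labelled as unique to yoga would point them in the wrong direction.

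**Working it through.** **Inputs from the protocol (section A).** Allocation is a "2:2:1 randomization ratio (yoga: exercise: self care), with a total of 210 participants". "Assuming 10% loss to follow-up", "there would be outcomes data for 75:75:38 participants in the yoga, exercise, and self care groups, respectively". The baseline-adjusted RDQ SD is 3.68. Of the alpha the section says that "both primary outcomes (function and symptoms) will be tested at the 0.05 level"; two-sided is assumed. Mediation power for yoga v self care is 0.86.

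**Step 1: reproduce the plan's own power.** For 2.5 RDQ points with 75 v 38 participants:

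- SE = 3.68 × √(1/75 + 1/38) = 3.68 × 0.1991 = 0.733
- 2.5 / 0.733 = 3.41, and power = Φ(3.41 − 1.96) = 92.7% (92.3% with the noncentral t)

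The protocol states 92%, so it reproduces. The mediation powers of 0.86 and 0.83 cannot be reproduced, because the path sizes behind them are not given. The 0.86 is therefore taken as an input.

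**Step 2: bound for an equally shared mediator.** If both classes act identically through the mediator, both tests have power *p*. Treating them as independent, P(yoga significant, exercise not) = *p*(1 − *p*) = 0.86 × 0.14 = 12.0%. The two comparisons share the self care arm, so their results are positively correlated and this is an upper bound.

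**Step 3: simulation of an equally shared mediator.** The arms were 75:75:38, with RDQ SD 3.68, a 2.5-point benefit for both classes and identical mediator paths (assumed sizes). Mediation was judged by joint significance of the two paths, as a stand-in for the weighted model, with 8,000 runs per setting. Ranges cover results with and without restriction to Scenario 3.

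| Model | Mediation power | Yoga significant, exercise not | Exercise not significant, given yoga significant |
|---|---|---|---|
| Three-arm | 0.845–0.877 | 6.2–7.4% | 7.2–8.7% |
| Pairwise | 0.836–0.873 | 7.1–11.4% | 8.2–13.6% |
| Three-arm | 0.713–0.734 | 10.7–11.5% | 14.5–16.1% |
| Pairwise | 0.673–0.734 | 12.9–14.9% | 18.6–20.5% |
| Three-arm | 0.520–0.609 | 9.1–13.8% | 14.9–26.6% |
| Pairwise | 0.458–0.513 | 15.0–18.2% | 29.2–39.7% |

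A direct test of the difference, in the three-arm model, gave a false result in 3.8–5.0% of trials over both directions, so about 2–2.5% in the yoga-only direction.

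A second simulation used the weighting approach itself, with a percentile bootstrap (300 resamples) and 1,000 Scenario 3 trials per setting. It assumed a mediator shift of 0.62 SD and a standardized slope of 0.40, which gave mediation power 0.83. The yoga-only verdict came up in 8.2% of trials. The direct bootstrap interval gave a false difference in 3.3% over both directions.

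**Step 4: a partly shared or truly unique mediator (weighting simulation).**

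| Exercise's mediated effect, as a share of yoga's | Yoga-only by the significance contrast | Difference found by direct interval |
|---|---|---|
| 75% | 22.8% | not run |
| 50% | 49.1% | 30.5% |
| 0% | 78.8% | 82.3% |

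The joint-significance test gave 25% and 53% for the 75% and 50% rows.

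**Step 5: several mediators.** These rates are per mediator, and Table 4 lists nine. For illustration only, three equally shared and independent mediators at 8% each give 1 − 0.92³ = 22% for at least one false yoga-only label.

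**The case against.** The strongest reply is that the passage is an illustration, worded tentatively as an example of what might happen, within an aim the protocol calls exploratory. The operative steps select mediators mainly by how much of the effect they explain, and the final model already yields indirect-effect estimates. What is missing is an interval for one contrast, which an analysis plan not shown here could supply.

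Much of this stands. A reader might infer that the protocol fixes a decision rule, or that a shared mediator would often be reported as unique to yoga. The documents support neither. At the only stated power (0.86), the yoga-only mislabelling of an equally shared mediator is about 6–12%. Higher rates need lower power or partial sharing, and both are assumptions. A count of discordant results in both directions (15.8% in the weighting simulation) would also overstate it, since it includes exercise-only verdicts.

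In the partial-sharing settings the two indirect effects really do differ, so only the claim of a yoga-only or completely different pathway is false. Hypothesis 2 concerns total effect and is untouched. The simulations also leave out the screening step, the 10% retention step, the multiple-mediator model and the repeated time points.

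The reply does not rescue the inference. The text says that this analysis will settle the question, and the one pattern it offers as evidence is invalid. That is a wrong statement on the page, beyond a detail left for later.

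**Conclusion.** The concern holds in this limited form: the only evidence pattern illustrated for Scenario 3 contrasts a significant with a non-significant result, and no comparison of the two indirect effects is stated.

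For an equally shared mediator the false yoga-only rate is roughly three to five times that of a direct test, at mediation power near 0.86. It is higher at lower power. If exercise has three quarters or half of yoga's mediated effect, a partly shared pathway would be labelled yoga-only in about a quarter or a half of trials.

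These figures rest on assumed path sizes, on equal 2.5-point benefits for both classes, and on simplified versions of the planned model. The point should be corrected, but it affects only an exploratory aim. No primary efficacy conclusion depends on it.

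**What to change.** Replace the Scenario 3 example with a direct comparison:

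- For each retained mediator, estimate the yoga v self care and the exercise v self care indirect effects on the same three-arm data.
- Report their difference with a 95% bootstrap interval, resampling participants within arm.
- Say that the pathways differ only if that interval excludes zero. Otherwise report the interval and say the trial could not tell whether the pathway is shared.
- Drop the absence of a significant change for exercise as evidence that exercise does not act through the mediator. Report its indirect effect with its interval.
- Say that the trial *will explore* whether pathways differ, in place of the claim that it can determine this.

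This is a change of wording and one extra contrast from models already planned. It needs no new data or participants. The downside is sensitivity: where exercise has half of yoga's mediated effect, a difference would be declared in about 31% of trials, against 49% labelled yoga-only by the significance contrast. For a mediator truly unique to yoga, little is lost (82% v 79%).

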## List of abbreviations

CAM: Complementary and Alternative Medicine; CATI: computer assisted telephone interviewing; CLIA: Clinical Laboratory Improvement Amendments (certification for US clinical laboratories); CONSORT: CONsolidated Standards of Reporting Trials; DHEA: Dehydroepiandrosterone; GEE: General Estimating Equations; ICD-9: International Classification of Diseases, 9^th ^edition/revision; IPW: Inverse Probability Weighted; IRB: Institutional Review Board; NCCAM: National Center for Complementary and Alternative Medicine; RDQ: modified Roland-Morris Disability Questionnaire; SD: Standard Deviation.
